#### Trial operation and maintenance of the system

Before the start of the study, a test operation of the system will be carried out in the participating households by the developer of the system. During the study, detailed calibration and inspection of the system will be regularly conducted to ensure the accuracy and reliability of the intervention and measuring results.

#### Data of the daily added salt intake integrity

Before the study, the participants will be informed that they will be provided with salt for free, which aims to make them use the added salt only from the smart salt checker container in the survey period. And the measured outliers will be excluded, which may be caused by using too much salt for preserving food, adding too much salt to the smart salt checker or other reasons. A certain reward will be given to the households’ main cooks who actively participate in the programme every month.

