**Fig. 1 Fig1:**
[figure not shown]
System functional structure diagram

The front-end sensing system is also called the “smart salt checker”. It has a salt container and an electronic salt sensor. The electronic salt sensor is equivalent to a self-designed electronic weighing scale on the base of the salt container, which can weigh the salt in the container, with a weighing range of 0–250 g and a sensitivity of 0.2 g. After the user takes the salt each time, and the container is placed on the base with the lid closed, the processing unit of the electronic salt sensor can immediately detect and record the weight and the time of salt used.

The cloud analysis system can automatically calculate the individual added salt intake of each household member according to the information acquired from the terminal interaction system. The daily added salt intake of each household member will be calculated on the basis of the distribution of staple food consumption of residents in the household. Daily intake estimates of added salt for each household member (g/standard) = (30 days’ intake of added salt by the surveyed household × standard daily number of each member in the household/standard daily number of all people in the household)/30 [39].

The terminal interaction system is a salt-limiting WeChat mini programme; through the programme, basic data can be acquired of the participating household’s main cook and other household members, such as their age, gender, occupation, marital status, education level, height, weight, labour intensity, health status, the number of people per meal and meal ratio per day for members aged>2 years old in their household. Participants with hypertension will also be encouraged to provide data on blood pressure, and the time and tool of blood pressure measurement.

Overall, the SALTCHECKER contains three key features: (1) self-monitoring: to automatically calculate the daily added salt intake of each household member, (2) questionnaires: to investigate the basic demographic information of the household’s main cook and other household members and salt consumption-related KAP of the household’s main cook, (3) personalised reports: through salt-limiting WeChat mini programme, professional nutrition experts in our research group will provide the daily added salt intake of each household member and corresponding healthy salt-using suggestions for specific household members to the household’s main cook.

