#### Randomization and blinding

After the baseline survey, 600 participating households’ main cooks will be randomly divided following a 1:1 ratio into the intervention group and the control group by the household demographic information, with 300 households in each group. The study coordinator will be responsible for the randomization and verification of the computer-generated intervention assignment with a randomization table. All the investigators, except for the study coordinator, will be blinded. The participants will be blinded and instructed not to inform the other participants of the treatment they receive.

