#### Primary outcomes

Daily added salt intake of each household member, assessed at baseline, 3 and 6 months.Salt consumption-related KAP of the household’s main cook, assessed at baseline, 3 and 6 months.

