## Discussion

This study will be the first to apply IOT technology to monitor and control the added salt intake in Chinese households. We expect to find that the salt consumption-related KAP score will be higher and the daily added salt intake of each household member will be less in the intervention group than in the control group. In the intervention group, we also expect that the time trend of the daily added salt intake of each household member will show an overall downward trend. A stronger reduction is expected in salt over-consumption households, and the strength of the effect is expected to be higher between 3 months and baseline than between 6 months and baseline and between 6 and 3 months due to time effect [16]. We speculate that if the monitoring system is used continuously after 6 months, the salt consumption-related KAP of the household’s main cook will improve continuously or be maintained at a good level, and the daily added salt intake of each household member will decrease continuously or be maintained under the recommended level of the Chinese Nutrition Society (6 g/d) [3]. In addition, the demographic characteristics may be factors that influence the SALTCHECKER effect.

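### Salt readings are excluded because their value is extreme, with no stated check of the cause, so genuine heavy intake can be dropped after randomisation and the mean difference is likely to shrink

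*Protocol article*

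**What the plan says.** The rule is in the protocol article, under Quality control, in the paragraph on the integrity of the added-salt data: "the measured outliers will be excluded, which may be caused by using too much salt for preserving food, adding too much salt to the smart" device. The sentence closes with an unspecified category of other reasons. It gives causes only as possibilities and describes no step that establishes the cause before a reading is dropped.

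The data concerned are a primary outcome: "Daily added salt intake of each household member, assessed at baseline, 3 and 6 months". Under the development of the system, this outcome is built from "30 days’ intake of added salt by the surveyed household", shared among members and divided by 30.

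On timing, Randomization and blinding states: "After the baseline survey, 600 participating households’ main cooks will be randomly divided following a 1:1 ratio". The 3- and 6-month readings therefore arise after allocation. The same section adds: "All the investigators, except for the study coordinator, will be blinded".

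The Discussion gives two expectations that matter here. One is that "the daily added salt intake of each household member will be less in the intervention group than in the control group". The other is that "A stronger reduction is expected in salt over-consumption households".

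**The concern.** The rule selects on the outcome itself. Salt use cannot fall below zero and is likely to be right-skewed, so common outlier rules mostly remove high readings. Some of these will be salt drawn for preserving food or handling errors, and removing them is reasonable. Nothing in the sentence separates them from a household that simply eats a lot of salt.

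If the intervention lowers intake, the control arm has more readings above any common cut. It then loses more of its upper tail, its mean falls further, and the estimated difference moves towards zero. The expectation of a stronger reduction among over-consuming households makes this worse, because more of the effect then lies near the tail being trimmed. Absolute intake is also understated in both arms. None of this depends on how excluded days are counted.

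**Working it through.** **The plan's own figure.** The protocol attaches no number to the exclusion. Its one computed figure, the sample size, reproduces: (1.96 + 1.28)² × 2 × 0.42 × 0.58 / (0.46 − 0.38)² = 10.4976 × 0.4872 / 0.0064 = 799.1, against 799 stated. It is used here only for its inputs: 38% and 46% of people at or below 6 g/d.

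**Check 1: lognormal intake matched to those proportions.** The spread of added-salt intake is not given, so the coefficient of variation (CV) is an assumption, varied from 0.3 to 1.0. At CV 0.5:

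- Log-scale SD: s = √ln(1 + 0.5²) = 0.472.
- Log-scale location: μ = ln 6 − s·z(p). Control, p = 0.38: μ = 1.936. Intervention, p = 0.46: μ = 1.839.
- Means exp(μ + s²/2): 7.75 and 7.03 g/d; true difference 0.715 g/d.
- Mean of the values kept below a cut c: exp(μ + s²/2) × Φ[(ln c − μ − s²)/s] / Φ[(ln c − μ)/s].
- Common cut at mean + 3 SD (c = 18.54 g): 1.86% of control and 1.11% of intervention values go; the kept means are 7.47 and 6.86; the difference is 0.607, and 0.607/0.715 = 85% is kept.
- Common cut at Q3 + 1.5×IQR (c = 15.55 g): 4.36% and 2.77% go; the difference is 0.533, and 0.533/0.715 = 75% is kept.

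Over CV 0.3 to 1.0, the share kept is 91% down to 74% at 3 SD and 85% down to 53% at 1.5×IQR. Cuts set separately in each arm (3 SD or 1.5×IQR) keep 80–99%.

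**Check 2: daily readings.** Assumptions: control mean 6 g/d per person; 10% proportional reduction; lognormal household means (log-SD 0.3–0.5); day-to-day CV 0.5–1.0; 30 days; all readings genuine. Excluded days also leave the denominator, so the result does not depend on the fixed 30.

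| Cut | Share of true difference kept |
|---|---|
| Pooled, daily, Q3 + 1.5×IQR | 48–73% |
| Pooled, daily, mean + 3 SD | 72–85% |
| Within household, daily, 1.5×IQR | about 80–94% |
| Within household, daily, 3 SD | about 90–98% |

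One pooled example (log-SD 0.5, CV 0.5, 1.5×IQR): 6.2% of control and 4.5% of intervention readings are excluded, a true difference of 0.61 g/d becomes 0.42 g/d, and the control mean falls from 6.01 to 5.34 g/d (0.67/6.01 = 11%). With a within-household cut, exclusions are equal by arm (for example 4.1% and 4.1%) and the relative reduction stays at about 10%; only the absolute difference shrinks.

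**Check 3: extremes that are artefacts.** Take Check 1 at CV 0.5 and add 30–100 g to 1–3% of records, equally in both arms. A wide cut (above 30 g, or mean + 3 SD) keeps about 98–99% of the difference and raises the standardised difference from 0.06–0.09 to 0.16–0.19. A 1.5×IQR cut still keeps only 76–78%, because it also removes genuine values.

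**Power.** In Check 1 at CV 0.5 the standardised difference is 0.192 with all values and 0.179–0.192 after the cuts tried. The SD shrinks along with the difference, so the damage is to the estimate.

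**The case against.** The strongest reply is that the sentence is a data-integrity measure. Salt drawn for preserving is household use but not that day's dietary intake, and overfilling is a handling fault that need not even produce a high reading. Removing either brings the measurement closer to the outcome. That stands, and the fix keeps both exclusions.

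A reader might infer that the protocol sets out to delete genuine heavy users. It does not say so; genuine intake enters only through selection by value and the catch-all. Nor do the documents support certain shrinkage with more control readings lost: that needs a cut common to all households. A within-household screen would fit the spike-type events named and would exclude equally by arm.

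A reader might also model the benefit as confined to over-consuming households, which gives far larger losses. The Discussion says only that the reduction is stronger there. Over-consumers are not the same as outliers either: under the sample-size assumption, 100 − 38 = 62% of people exceed 6 g/d without the intervention, whereas the simulated cuts remove at most 8.4% of readings.

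Finally, the cut-off, its unit and any sensitivity analysis may be in an analysis plan that is not shown. Their absence is not the point. The article itself fixes value as the trigger, and a plan that added only a numerical threshold would keep the problem. Blinding does not cure it, because a common cut applied blind still removes more readings from the arm with higher intake.

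**Conclusion.** The point holds in a conditional form. A primary outcome observed after randomisation is cleaned by its own value, with open-ended causes and no stated check, so genuine high intake can be removed. With one cut across households and a working intervention, the mean difference is likely to be biased towards zero.

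The size cannot be fixed from the documents. If all readings are genuine, a pooled daily cut could cost from about 15% to about half of the difference, and a within-household 1.5×IQR cut about 6–20%. If the extremes are artefacts and the cut is wide, the cost is about 1–2%. These figures rest on lognormal intake, the assumed spreads and, for the daily readings, a 10% reduction. The consequence is mainly a biased estimate of effect, not a material loss of power.

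**What to change.** Replace the outlier sentence in the data-integrity paragraph with:

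> Readings are excluded only for a verified cause that means they do not measure dietary intake (device, refill or overfilling fault; salt withdrawal for preserving food, asked in the same way in both arms), by a rule fixed in advance and judged blind to arm. A high value alone may trigger a check but is not a reason for exclusion; all other readings stay in the primary analysis.

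Report the number of exclusions by arm and by reason, and give a sensitivity analysis with all readings kept. The cost is a change of wording, a short question to both arms, one extra analysis, and somewhat larger variance from the high readings that remain.

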### Analysis strategy

Statistical analyses will be conducted using SPSS version 22.0 (IBM Corp, Armonk, NY, USA). Descriptive statistics will be calculated for all the variables under examination. The counting data will be described by frequency and percentile, and the metrological data description will use mean, standard deviation and median. The demographic characteristics of the household members (e.g. age, gender, ethnicity, occupation, marital status, education level, height, weight and health status) will be analysed to examine the influencing factors of the household salt monitoring system by using multivariate regression analysis. Linear mixed models, generalized estimating equations (GEE) or t-test will be used to examine the predictors of added salt intake of each household member and salt consumption-related KAP of the household’s main cook and the moderators, mediators of the intervention effects. Correlation analysis will be used to test the link between the score of salt consumption-related KAP and daily added salt intake of each household member. Meanwhile, we will analyse the time trends of the daily added salt intake of each household member during the study period. The level of significance will be set at < 0.05. For the qualitative data analysis, the audio recordings will be transcribed verbatim by trained transcribers. Content analysis of the qualitative information gathered will be done using MAXqda. In addition, if there is enough data acquired about blood pressure, analysis of the impact of the system on blood pressure will be considered.

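### Member-level salt is a computed share of the weighed household total, so the planned predictor and moderator models cannot show that a member's trait predicts that member's salt

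*Protocol article*

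**What the plan says.** Under *The Development of SALTCHECKER*, the sensor weighs the salt in the household container. The cloud system will then "calculate the individual added salt intake of each household member according to the information acquired from the terminal interaction system". Intake is "calculated on the basis of the distribution of staple food consumption of residents in the household", and the formula multiplies the 30-day household total by the ratio "standard daily number of each member in the household/standard daily number of all people in the household" and divides by 30. The standard daily number is not defined further. The mini programme collects, for the cook and other members, "age, gender, occupation, marital status, education level, height, weight, labour intensity, health status, the number of people per meal and meal ratio per day".

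Under *Analysis strategy*, demographic characteristics of household members ("age, gender, ethnicity, occupation, marital status, education level, height, weight and health status") are to be analysed "to examine the influencing factors of the household salt monitoring system by using multivariate regression analysis". That sentence does not name its outcome. The next one does: linear mixed models, GEE or t-tests will "examine the predictors of added salt intake of each household member", and will also examine moderators and mediators of the intervention effect. The *Discussion* expects that demographic characteristics may influence the effect of the system.

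**The concern.** The outcome in the predictor models is not an observation on the member. It is an observation on the household, divided by a rule. If the rule uses a trait, or something related to that trait, a regression of the divided value on the trait partly returns the rule. The trial could then report that, for example, women or older members eat less added salt, when the difference was put there by the allocation. Standard errors clustered by household do not protect against this, because the problem is bias and not precision. A subgroup statement about who benefits most could arise in the same way.

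**Working it through.** The plan gives no figure for this point, so there is none to reproduce. The check starts from its formula.

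**1. What the formula implies.** Let S be the household's daily salt (30-day total divided by 30) and n_i the standard daily number of member i. Then x_i = S × n_i / Σn. For two members of one household, x_1 / x_2 = n_1 / n_2. S cancels, so the within-household contrast contains no salt measurement.

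**2. Overlap of outcome and regressors.** The analysis section lists nine traits. Eight of them (age, gender, occupation, marital status, education, height, weight, health status) are also among the mini-programme entries; ethnicity is not. The member calculation draws on those entries, but the article does not say which of them set n_i.

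**3. One couple.** Assumptions: 7 g/d per head, so S = 14; no true difference; man's weight 1.0; woman's weight q. The man gets 14/(1+q) and the woman 14q/(1+q).

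| q | man (g/d) | woman (g/d) | difference |
|---|---|---|---|
| 1.00 | 7.00 | 7.00 | 0 |
| 0.95 | 7.18 | 6.82 | −0.36 |
| 0.90 | 7.37 | 6.63 | −0.74 |
| 0.80 | 7.78 | 6.22 | −1.56 |

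**4. Across households.** The regression coefficient is smaller than in step 3, because the weights cancel in one-person and same-sex households. Simulation: 600 households (the planned number), mean size about 2.7 (the plan's census figure is 2.70), 200 runs, least squares with household-clustered errors. Typical intake of 7 g/d, spreads and weights are assumptions. There is no true gender effect in these runs:

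| assumption on the share | gender coefficient (g/d) | runs with p < 0.05 |
|---|---|---|
| ignores gender | about 0 | 2.5% |
| varies independently of traits | about 0 | 5.5% |
| female weight 0.95 | −0.24 | 34% |
| female weight 0.90 | −0.50 | 89% |
| female weight 0.80 | −1.07 | 100% |

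A second set of runs gave −0.23, −0.48 and −1.04 for the last three rows. With a true +20% in women and weight 0.80, the estimate was −0.63 g/d, the wrong sign. With a true −20% and equal weights it was −0.55 g/d. The direction is right, but it is well short of the roughly 1.4 g/d (20% of 7) put in.

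**5. Moderators.** Let the intervention cut household salt by an assumed 20% for everyone, with q = 0.80. S falls from 14 to 11.2, the man from 7.78 to 6.22 and the woman from 6.22 to 4.98. The reductions are 1.56 and 1.24, a false difference of 0.31 g/d. Across households the expected value is 0.20 × 1.04 = 0.21 g/d. Simulation gave +0.21, significant in 29% of runs. A rerun with the spreads of step 4 gave about the same size but a lower rejection rate, so the rate should not be generalised. On a ratio scale both members fall by 20% and nothing appears. With no treatment effect, the arm-by-gender term averaged −0.006 g/d and was significant in 4.5% of runs, about the nominal rate.

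**6. Choice of household outcome.** Compare two men with two women at S = 14 and q = 0.80. Per standard person the values are 14/2 = 7.00 and 14/1.6 = 8.75, a false +1.75 g/d. Simulation also gave about +1.75 for proportion female, significant in 100% of runs. Per head, both households have 14/2 = 7.00, and the simulated coefficient was about 0.

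**The case against.** The strongest objection is that the article never says age, gender or labour intensity set the share. The only basis it names is staple food consumption. The list of entered traits describes what the mini programme collects, and it includes items such as marital status that are unlikely inputs to a formula. The share could rest on meal counts and meal ratio alone. This stands, and it rules out a reading that a reader might infer: that the share is built from age, sex and labour weights and that the regression is therefore wholly circular. The documents do not support that. Nothing shows that education or marital status enters the share, ethnicity is not among the listed entries, and household totals are real measurements, so differences in composition between households carry information (the −0.55 g/d in step 4).

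It does not remove the point. If the share rests on meals or staple food, the within-household contrast describes meals or staple food and still not salt. Any trait related to that share will look like a salt predictor.

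Three further objections have weight. The sentence on influencing factors does not name member salt, so the point rests on the following sentence, which does. Randomization is by household, so no false moderator arises when the intervention has no effect. The *Discussion* concedes that member estimates may be inaccurate, but it does not mention that the error may be tied to the covariates. An article may leave the definition of an input to a fuller document. Here, however, both the allocation rule and the analysis are stated, and they do not fit together.

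**Conclusion.** The point holds in a limited form. Member salt is allocated, not measured, so the planned models cannot establish that a member's trait predicts that member's salt. A trait that enters the share or is related to it gets a main effect made at least partly by the formula, and a false moderator effect in g/d if the intervention works. The size cannot be read from the article. It runs from about 0 if the share is unrelated to the trait to about −1.04 g/d for gender at an assumed female weight of 0.80. The moderator figure (+0.21 g/d) also assumes a 20% reduction. Very small p-values are a consequence of strong assumed weights and not a general prediction. The predictor and moderator analyses are affected; the randomized comparison of household salt is not.

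**What to change.** Run the predictor and moderator analyses on the weighed household total, either with household size or unweighted person-meals as a covariate or offset, or per head. Do not use salt per standard person-day, because its denominator is the same share weight (step 6). Use household-level and main-cook covariates. State which entered items set the standard daily number. If member-level models are still shown, do not interpret coefficients for traits that enter or determine that number.

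The cost is a change of wording in the analysis section; no new data are needed. The downside is that member-level demographic predictors of salt can no longer be reported.

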### Study sample

To calculate sample size, the following formula will be used:

$$ N=\frac{{\left({U}_{\alpha }+{U}_{\beta}\right)}^2\times 2P\left(1-P\right)}{{\left({P}_1-{P}_2\right)}^2} $$

where α = 0.05, β = 0.1, and then U_0.05_ = 1.96, U_0.1_ = 1.28. According to a previous study in China, the proportion of daily per capita salt consumption ≤6 g was 37.91% and the proportion increased to 45.91% after using salt-control spoons in participating households [16]. Thus, in this study, the increase in low salt consumption (≤6 g/d) with SALTCHECKER from about 38% (*P*_*1*_) to some 46% (*P*_*2*_), *P* = (*P*_1_ + *P*_2_)/2 = 0.42 was assumed. The sample size is calculated to be 799 cases. According to some similar salt-limiting trials, the dropout rate was 0.5–5% [18, 40–42]. And sampling error and invalid questionnaires may be 10–15%. Therefore, it was assumed 10–20% should be added on the basis of the estimated sample size, so 879–959 participants will be needed. The data of the tabulation on the 2010 population census of the People’s Republic of China (No. 1) indicated that the average household size in Chongqing is 2.70 (person/household) [43]. Therefore, 300 households’ main cooks in each of the intervention group and control group will be investigated in this study.

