## Trial status

The project is planned from January 2019 until December 2020. The recruitment phase of this study is scheduled from January 2020 to March 2020. The intelligent household added salt monitoring system will be developed and improved from January 2019 until December 2019. The daily added salt intake of each household member will be monitored from April to September and the salt consumption-related KAP of the household main cook will be investigated in April, July and October 2020. Data analysis and evaluation will be performed after September 2020. The protocol stands at version 3.0 on 10 March 2020.

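### The test of the KAP–salt link is an unadjusted correlation with each member's salt; if arms or household members are combined, it rejects above its nominal 5% with no link within arm

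*Protocol article*

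**What the plan says.** The Analysis strategy section of the protocol article gives this question one sentence: "Correlation analysis will be used to test the link between the score of salt consumption-related KAP and daily added salt intake", taken for each household member. It is framed as a test, and the same section adds "The level of significance will be set at < 0.05". The sentence does not say which arms, visits or records enter. The sentence on modelling in the same section names linear mixed models, GEE or a t-test for predictors of salt and KAP and for moderators and mediators; correlation is then named separately for the KAP–salt link.

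Three other places bear on it:

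- The Discussion expects that in the intervention group "the salt consumption-related KAP score will be higher and the daily added salt intake of each household member will be less" than in the control group.
- The section on the development of SALTCHECKER derives each member's daily salt as a share of one 30-day household total, split by standard daily numbers. The KAP score belongs to the main cook alone, so all members of a household share it.
- Under Primary outcomes, both measures are assessed at baseline, 3 and 6 months. Trial status gives the calendar: "The daily added salt intake of each household member will be monitored from April to September", while the cook's KAP "will be investigated in April, July and October 2020".

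**The concern.** There are two separate problems.

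1. **Arm as a common cause.** The intervention is meant to move both variables, KAP up and salt down. If the two arms are put into one correlation, the difference between arm means alone produces a negative coefficient, whether or not cooks with better KAP use less salt within either arm. Pooling visits lets time act in the same way.

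2. **Records that are not independent.** The sentence correlates a score held once per household with a salt value held once per member, and the members' values are shares of one total. An ordinary correlation test counts each household two to three times. Pooling visits repeats the household again.

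At stake is how a secondary result is interpreted. The Background uses a relation between knowledge, attitude and behaviour as rationale, so a significant coefficient invites the reading that better KAP goes with lower salt. It could reflect only that the arms differ, or that households were counted several times. The comparison of the arms is not affected.

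**Working it through.** **Inputs from the protocol article.** There are 300 households per arm, 600 in all (Randomization and blinding). Average household size is 2.70 (Study sample), so 600 × 2.70 = 1,620 members. The salt effect is "the increase in low salt consumption (≤6 g/d) with SALTCHECKER from about 38"% to 46% (Study sample). The section also has "where α = 0.05, β = 0.1, and then" a normal quantile of 1.96, which is two-sided.

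**Assumed, because the article gives no figure.** KAP shift dK of 0.2, 0.5 or 0.8 SD; a larger salt shift of 0.5 SD as a contrast; correlation of 0.5 between visits of one household, for KAP and for salt; intraclass correlation of 0.8 for salt between members.

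**Plan's own figure.** (1.96 + 1.28)² × 2 × 0.42 × 0.58 / 0.08² = 799.1, which reproduces the stated 799. The article gives no figure for the correlation analysis.

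**Salt effect in SD units.** If intake is normal, 38% to 46% is a shift of dS = −0.100 − (−0.305) = 0.205 SD.

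**Correlation produced by arm alone.** With 1:1 allocation and no link within arm,

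r = −(dK × dS / 4) / √[(1 + dK²/4)(1 + dS²/4)].

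For dS = 0.205 this is −0.010, −0.025 and −0.038 at dK = 0.2, 0.5 and 0.8.

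**One visit, one record per household, n = 600.** The test statistic is centred near |r| × √597. For dK = 0.5: 0.0247 × 24.43 = 0.60, and P(Z > 1.36) + P(Z < −2.56) ≈ 9%. For dK = 0.8: 0.0379 × 24.43 = 0.93, giving about 15%. Simulation with 2,000 runs per setting agrees:

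| Salt shift (SD) | KAP shift (SD) | Arms combined, one visit | Three visits pooled (1,800 records) | 1,620 members as independent | Arm means removed, one record per household |
|---|---|---|---|---|---|
| 0.205 | 0 | 4.9% | 10.7% | 21.0% | 4.8% |
| 0.205 | 0.2 | 5.3% | 13.8% | 22.4% | 4.4% |
| 0.205 | 0.5 | 10.4% | 22.2% | 30.1% | 5.2% |
| 0.205 | 0.8 | 14.6% | 33.0% | 40.8% | 4.5% |
| 0.5 | 0.5 | 32.1% | 58.6% | 61.3% | 4.6% |
| 0.5 | 0.8 | 60.9% | 89.5% | 85.0% | 5.1% |

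**Check of the three-visit column.** With dK = 0, independence is still violated. The variance of the coefficient is inflated by 1 + 2 × 0.5 × 0.5 = 1.5, so the rejection rate is 2 × P(Z > 1.96/√1.5) = 2 × P(Z > 1.60) ≈ 11%. Part of the 22% to 33% is therefore repeated records and part is the arm effect.

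**Check of the member column.** Take 70% of households with three members and 30% with two (mean 2.7). The sum of squared sizes is 420 × 9 + 180 × 4 = 4,500. The inflation is [1,620 + 0.8 × (4,500 − 1,620)] / 1,620 = 3,924 / 1,620 = 2.42. The rejection rate is 2 × P(Z > 1.96/√2.42) = 2 × P(Z > 1.26) ≈ 21%, with no effect on KAP at all.

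**Calendar.** Counting from April, October is month 6. The last 30-day salt window, September, comes directly before the October survey.

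**The case against.** The strongest reply is that the sentence does not say arms or visits are combined. A correlation at baseline, or within one arm at one visit, would not carry the arm effect. Which records enter a secondary correlation is ordinary detail for an analysis plan, and this is a condensed article. That stands as far as it goes, and it makes the arm part of the point conditional. It does not answer the household part: the sentence itself names each household member, and within one arm at one visit the members would still share one cook's score and one household total.

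A second reply is that a link means association. If the programme moves both measures, the marginal association is real, and rejecting is no error. This is correct for a marginal null. But that association tells the reader nothing beyond the two arm comparisons, and it does not bear on whether cooks with better KAP use less salt. The rates above are errors against the null of no link within arm, which is the informative one.

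A third reply is that mixed models and GEE are already in the plan for predictors and mediators. They are, which makes the repair cheap, but the plan assigns correlation to this link.

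Two stronger readings are tempting and unsupported. A reader might infer that a spurious link is bound to be declared. At the protocol's own salt effect and one visit, the rate is 5% to 15%, so most such trials would declare none; the high figures need larger shifts or records wrongly treated as independent. A reader might also infer that the October survey, coming after monitoring ends in September, produces a false link. It does not: it matches the 6-month visit and follows the last salt window, and a lag would if anything weaken a correlation. It limits only the direction in which the 6-month pair can be interpreted.

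**Conclusion.** The point holds as a conditional weakness of a stated method for a secondary analysis. If arms are combined, a test at nominal 5% rejects in about 10% to 15% of trials at one visit, and about 22% to 33% with three visits pooled as independent records, when there is no link within arm. These figures rest on the protocol's salt effect read as 0.205 SD under normality, on assumed KAP shifts of 0.5 to 0.8 SD and, for the pooled figures, on an assumed between-visit correlation of 0.5. With a KAP shift of only 0.2 SD the single-visit rate is 5.3%, so the arm part is then negligible. Using each member as an independent record gives about 21% with no KAP effect, at an assumed intraclass correlation of 0.8, whether or not arms are combined. With one record per household and arm means removed, the rate returns to about 5%. The change should be made, but it does not touch the test of effectiveness.

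**What to change.** Replace the correlation test with a linear mixed model or GEE of added salt on the cook's KAP score, adjusted for arm and visit. Use one household salt value per visit with repeated visits clustered by household or, if member values are kept, cluster them by household too. State which 30-day salt window is paired with each KAP survey, for example September salt with the October survey, and reconcile the Trial status calendar with the visits under Primary outcomes. All three KAP surveys and the 3-month salt data can stay in the model. Correlation coefficients may still be reported by arm and visit as description. State that the result is an association and does not show that better KAP lowers salt.

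The cost is a change of wording. No new data are needed, and the models are already named in the section. The adjusted association will be smaller and less precise than the unadjusted one.
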